### Information disclosure

The study was registered in the public UMIN clinical trials registry. The results will be presented at the Japanese Orthopaedic Association Annual Meeting, and we intend to submit them to an orthopedic journal. Data that will be presented will only consist of those that have been processed statistically; thus, personal health information of the study subjects will not be made available.

### Safety and adverse events

We do not anticipate problems that are detrimental to the participants. However, in the event of a serious adverse event (SAE), the principal investigator will take necessary measures, report to the hospital director, and share information with study investigators. Any unexpected SAE that occurs during the course of the study will be reported to the hospital director, study team members, and the Ministry of Health, Labor and Welfare in Japan. Actions taken in response will be announced.

### Statistical analysis

Chi-square test will be used to compare the presence of LFCN injury. We will perform a normality test using Shapiro-Wilk to detect parametric or nonparametric data. To assess the effect of LFCN injury on patient QOL to compare differences in the PRO assessments between lateral and conventional approach, the Mann-Whitney *U* test will be used if data is non-parametric, and the *t*-test will be used if data is parametric.

*P* < 0.05 will be considered significant. We will also present treatment effects and confidence intervals and perform adjusting for confounding factors as an exploratory analysis using logistic regression or multiple regression. Statistical analyses will be performed using SPSS software version 22 for Mac (IBM Corp., Armonk, NY, USA).

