### Sample size

A sample size of 144 subjects is planned. According to our previous study, the overall incidence of LFCN injury incidence after DAA for THA is 42%, and the incidence of non-fan variation is 28.6% [16]. Thus, we hypothesize the lateral DAA approach will reduce the rate of LFCN injury to 10%. Using an alpha error of 5% and a power of 80% in two-tailed analysis, 124 subjects need to be recruited. These calculations were performed using SAS software version 9.4 (SAS Institute, Cary, NC, USA). Considering the dropout, we will enroll a minimum of 72 patients in each group.

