#### Secondary outcomes

The secondary outcome will be assessed based on patient-reported outcomes (PROs) at 3 months after surgery in an outpatient setting to examine the extent to which LFCN injury has affected the patient’s quality of life (QOL) and complications (dislocations, infections, or intraoperative and periprosthetic fracture).

PROs will be evaluated using the Western Ontario and McMaster Universities Osteoarthritis Index (WOMAC) (pain, stiffness, and function subscales), the Japanese Orthopaedic Association Hip-disease Evaluation Questionnaire (JHEQ), and the Forgotten-Joint Score-12 (FJS-12).

The WOMAC was first described by Bellamy and Buchanan in 1986. It uses a scoring system with a total score of 0 (poor) to 96 (excellent) and has since been used worldwide to evaluate hip and knee osteoarthritis. The JHEQ is a self-administered questionnaire for evaluating hip disorders in the Japanese population with a total score of 0 (poor) to 84 (excellent). The FJS-12 is a self-administered questionnaire measuring the PROs on the ability of the patient to forget about their prosthetic implant in everyday life and has a total score of between 0 (poor) and 84 (excellent) [26]. The lowest and highest scores for WOMAC are 0 and 96, whereas those of JHEQ are 0 and 84; thus, the lowest and highest scores for each questionnaire will be converted to 0 and 100.

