### Sample size

According to previous studies, the incidence of LFCN injury due to THA with the DAA is 28.6% in non-fan variation patients [16]. Therefore, we hypothesize the lateral DAA approach will reduce the rate of LFCN injury to 15%. Using an alpha of 5% and a power of 80% in two-tailed analysis, 130 subjects need to be recruited. These calculations were performed using SAS software version 9.4 (SAS Institute, Cary, NC, USA). As we expect a 10% dropout rate, we will enroll a minimum of 144 patients in each group.

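### The quality-of-life aim is stated as the effect of LFCN injury, but the only PRO comparison defined is between surgical approaches, which does not estimate that effect

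*Protocol article*

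**What the plan says.** Under Secondary outcomes, the protocol article gives the purpose of the 3-month PROs (WOMAC, JHEQ, FJS-12) as "to examine the extent to which LFCN injury has affected the patient" in terms of quality of life.

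The Statistical analysis section repeats that purpose and attaches a comparison to it: "To assess the effect of LFCN injury on patient QOL to compare differences in the PRO assessments between lateral and conventional approach". The test is Mann-Whitney or t, depending on a normality check. The grouping variable is the surgical approach.

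The only other analysis that could bear on the question is the statement that the team will "perform adjusting for confounding factors as an exploratory analysis using logistic regression or multiple regression". It names neither the confounders nor LFCN injury as an exposure.

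The expected injury rates come from the two Sample size sections. Both take 28.6% for the conventional arm ("the incidence of LFCN injury due to THA with the DAA is 28.6% in non-fan variation patients"). The section after Eligibility criteria assumes 10% in the lateral arm; the section after Secondary outcomes assumes 15%.

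**The concern.** The aim asks whether patients with an injured nerve report worse outcomes than patients without one. The planned test asks whether patients randomised to one fasciotomy site report different outcomes from those randomised to the other. By the protocol's own rates, most patients in both arms will be uninjured, so the arms differ only modestly in the exposure that the aim is about.

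The Background says that several studies found no effect of LFCN injury on hip function but that sensory disturbance may affect satisfaction. Whether injury matters to patients is therefore part of the trial's rationale. If the plan is followed as written, a result about approach is produced under a label about injury. A null arm difference would say little about the effect of injury, and a positive one could not be attributed to injury without further assumptions.

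**Working it through.** **Plan's own figure.** There is none to reproduce. The article gives no effect size, SD or power for the PROs. Every PRO effect size below is an assumption.

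**Inputs from the document.**
- Conventional-arm injury rate: 28.6%.
- Lateral-arm injury rate: 10% or 15%.
- 1:1 allocation, two-sided 5% level.
- Total size: the two Sample size sections disagree. I use 130 (the requirement in the later section) and 288 (its enrolment figure of 144 per group × 2) as a low and a high case.

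**Step 1: dilution.** Suppose injury shifts a PRO by d SD and approach affects PROs only through injury. The expected arm difference is then d × (conventional rate − lateral rate).
- 10% lateral rate: 0.286 − 0.100 = 0.186, so 0.186d; 1/0.186 = 5.4-fold.
- 15% lateral rate: 0.286 − 0.150 = 0.136, so 0.136d; 1/0.136 = 7.4-fold.

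For d = 0.5 SD the expected arm difference is 0.093 or 0.068 SD. Any direct effect of the fasciotomy site on PROs would be added to this, and the arm contrast would then not isolate injury at all.

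**Step 2: group sizes by injury status.** Expected injured = (N/2) × (sum of the two rates).
- N = 130, 10% rate: 65 × 0.386 = 25.1, about 25 versus 105.
- N = 130, 15% rate: 65 × 0.436 = 28.3, about 28 versus 102.
- N = 288, 10% rate: 144 × 0.386 = 55.6, about 56 versus 232.
- N = 288, 15% rate: 144 × 0.436 = 62.8, about 63 versus 225.

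**Step 3: power.** Two-sample non-central t, two-sided 5%, with non-centrality = difference in SD units × √(n₁n₂/(n₁+n₂)). Each cell gives power by arm / by injury status.

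| Assumed d | N=130, 10% rate | N=130, 15% rate | N=288, 10% rate | N=288, 15% rate |
|---|---|---|---|---|
| 0.2 SD | 6% / 15% | 5% / 15% | 6% / 27% | 6% / 29% |
| 0.3 SD | 6% / 27% | 6% / 29% | 8% / 52% | 6% / 55% |
| 0.5 SD | 8% / 61% | 7% / 64% | 12% / 92% | 9% / 94% |
| 0.8 SD | 13% / 95% | 9% / 96% | 24% / >99% | 15% / >99% |

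The by-injury figures are unadjusted. Allowing for the extra spread that injury itself creates within each arm lowers the by-arm figures by at most about 2 percentage points.

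**Step 4: the same point as a sample size.** Detecting an injury effect of 0.5 SD through the arm contrast with 80% power needs 2 × (1.960 + 0.842)² / (0.5 × 0.186)² ≈ 1,815 per arm, or about 3,395 per arm with 0.136 in place of 0.186. Both are far beyond either stated enrolment.

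**The case against.** **The sentence may intend two aims.** It has two infinitive clauses and no conjunction. Inserting an "and" would give an injury aim and an approach aim, with the same tests serving both. This is a fair reading, and it removes any certainty that the authors meant the arm test to answer the injury question. But only one grouping is defined, and Secondary outcomes gives the injury aim alone, so the text still needs correcting.

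**The arm comparison is sound.** The Abstract lists the PROs as secondary endpoints without tying them to injury, and the trial's purpose is the effect of fasciotomy position. A reader might infer that the comparison is wrong and should be replaced. The document does not support that: it is the proper randomised analysis of approach on PROs and should stay.

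**The planned regression may cover it.** Multiple regression is promised as exploratory, and an injury model could sit there. Covariates can be left to an analysis plan. The exposure of interest is a different matter: the article sets a grouping for this aim, and it is not injury.

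**The power contrast can mislead.** A reader might take 8% against 61% as two versions of one test. They are different estimands, one randomised and one open to confounding. The effect sizes are assumed, and the prior studies cited in the Background make small effects plausible; at 0.2 SD the injury contrast is weak as well (15% to 29%). This stands.

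**Misreading is not stated.** Nothing in the article says that a null arm result will be presented as showing no effect of injury. That is a risk of the wording, not a stated intention.

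The choice of test by a normality check is a separate matter and adds nothing to this point.

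**Conclusion.** The concern holds for the secondary PRO aim. As written, the plan states a question about LFCN injury and defines a comparison of approaches, which does not estimate the injury effect. The 5.4- and 7.4-fold dilution rests on two assumptions: that the planning rates hold, and that approach affects PROs only through injury. If the second fails, the arm contrast is a worse guide to the injury effect, because a direct effect of the fasciotomy site is mixed in. Across assumed injury effects of 0.2 to 0.8 SD, both lateral rates and totals of 130 to 288, power by arm stays between about 5% and 24%.

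The primary endpoint and its test are unaffected. The point should be fixed because the stated secondary quantity is otherwise not estimated and the remedy is cheap.

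**What to change.** Split the sentence in Statistical analysis into two analyses and align the purpose clause in Secondary outcomes:

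- **(a) PROs by randomised approach**, lateral versus conventional, reported as the effect of approach.
- **(b) PROs by LFCN injury status at 3 months**, by multiple regression adjusted for arm and prespecified baseline factors, labelled observational and exploratory.

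State that any conclusion on how injury affects quality of life is drawn from (b) only, and that a null result in (a) is not read as absence of an injury effect.

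The cost is revised wording and one regression per PRO score on data already collected; design, recruitment and follow-up do not change. The downside is that (b) is open to confounding and has low power for small effects. Injury and PROs are also both self-reported at 3 months, and the injury definition includes thigh pain, so part of any association may reflect overlap in what is measured. The report should say so.

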### Data protection

In order to protect the confidentiality of personal health information, a study ID that does not contain any identifying information will be assigned to each subject. The principal investigator will follow the Standard Operating Procedures for the Storage of Materials and Information in Medical Research with Human Subjects. All data will be stored electronically or within the Orthopedics Department of our hospital for 5 years from the end (or after termination) of the study. Upon completion of this 5-year period, all documents will be deleted or discarded appropriately.

### Monitoring

Annual monitoring will be performed by the Clinical Research and Trial Center of Juntendo University, Japan, according to the Standard Operating Procedures for Monitoring and Audits in Medical Research with Human Subjects. Monitoring will be independent from conflicting interests.

### Audits

Monitoring and audits will be performed according to the Standard Operating Procedures for Monitoring and Audits in Medical Research with Human Subjects of the Clinical Research Support Center.

The institutional Research Ethics Board will review the study on an annual basis and evaluate whether the study activities can continue. Amendments to the study documents will be submitted each time and approved by the Research Ethics Board. If any severe adverse events are identified within the hospital, the study team will report to the Hospital Director immediately. The Research Ethics Board will then determine whether the study activities need to be terminated.

## Discussion

Surgical approaches for the placement of a hip prosthesis are classified as posterior, lateral, or anterior. DAA and ALA are anterior approaches that do not involve dissection of the tendon to reach the hip joints. Thus, they have advantages over other approaches in terms of functional recovery following the placement of a hip prosthesis [3, 14, 18, 27, 28]. Although both DAA and ALA are intermuscular approaches, ALA is associated with a risk of motor paralysis as it involves approaching between the tensor fasciae latae and gluteus medius, which are supplied by the superior gluteal nerve [22, 23]. On the other hand, the risk of motor paralysis is minimal in DAA as it is the only approach that involves the inter-innervated area where the sartorius and tensor fasciae latae muscles are supplied by the femoral and superior gluteal nerves, respectively [23, 29]. Thus, we selected DAA over ALA for the purpose of this study.

Rudin et al. reported three patterns of LFCN distribution (sartorius-type, posterior-type, and fan type) in an anatomical study and reported that LFCN injury is unavoidable in patients with a fan-type distribution if conventional DAA is used [15]. In our previous study, LFCN injury was observed after surgery in 9 of 10 patients with the fan type based on the ultrasound findings before THA (positive predictive value: 90%); however, no LFCN injury was observed in 25 of 26 patients judged as non-fan type (specificity: 96.2%). These findings suggest that ultrasonography is useful for evaluating LFCN distribution [16]. However, there is no study to detect a fan or non-fan type of LFCN. This will be a limitation.

In order to prevent LFCN, an incision for DAA is generally made outside of the space between the sartorius and tensor fasciae latae muscles. However, 42% of our patients developed LFCN injury [16]. In a subsequent study, we excluded fan type LFCN based on ultrasound findings because injury to fan type LFCN is considered unavoidable. We reported injury to non-fan type LFCN in 28.6% of patients [16]. Based on pathological findings, Ropars et al. suggested that damage to the nerves can be prevented by approaching as laterally and distally as possible [30]. We hypothesize that the risk of injury to non-fan variation LFCN may be reduced by an approach that is similar to ALA whereby the incision is made further away from the location where it is typically performed in conventional fasciotomy. The patients will be blinded by placing the skin incision in the same position in both groups although the position of fascia incision is different. The surgeon cannot be blinded, but the statisticians, participants, follow-up observers, and data analysts will be blinded. If this approach is successful at preventing nerve injury, it will overcome one of the few limitations of DAA. We believe that this will be greatly beneficial to patients undergoing THA.

## Trial status

We were actively recruiting at the time of submission. Patient recruitment started on June 2019 and the study was scheduled for completion in March 2021. The date of enrolment of the first participant to the trial was 3 June, 2019. This protocol is version 1.0, dated 20 February, 2019. The study is scheduled for completion in March 2023.

## Data Availability

The datasets generated and analyzed during this study are available from the corresponding author upon reasonable request. The informed consent form and other related documents are also available from the corresponding author upon request. This trial does not include collection of biological specimens.

## Abbreviations

THA: Total hip arthroplasty
DAA: Direct anterior approach
LFCN: Lateral femoral cutaneous nerve
BMI: Body mass index
QOL: Quality of life
PROs: Patient-reported outcomes
WOMAC: Western Ontario and McMaster Universities Osteoarthritis Index
JHEQ: Japanese Orthopaedic Association Hip-Disease Evaluation Questionnaire
FJS-12: Forgotten-Joint Score-12
